### Economic evaluation

The health economic evaluation is conducted in agreement with the CHEERS statement [35]. Healthcare utilization is measured and costs are calculated using standard unit prices (for the reference year 2014) published in the Dutch costing guideline [36]. In addition, data on (increased or decreased) productivity due to changes in the number of hours worked per week and accounting for absenteeism and presenteeism are valued using the mean per-capita gross income. The difference between ZemCAD and CAU in terms of health gains are expressed in QALYs, based on the EQ-5D. Non-parametric bootstrapping is used to estimate the uncertainty surrounding costs and effects. On that basis, probabilistic statements can be made about the likelihood that, relative to usual care, the new intervention (1) costs more and is associated with QALY gains, (2) costs more and is associated with QALY losses, (3) costs less and is associated with QALY losses, or (4) costs less and is associated with QALY gains. Obviously scenario 2 is the least attractive and in that case maintaining the old (current) health care system is the best option as seen from a (narrow) health-economics perspective, but always contingent on further medical-ethical considerations. In case of scenario 4 the new health care system is the best option as viewed from a health-economics perspective. However, we often end up in scenario 1: we pay more and get more QALYs. This could be an acceptable scenario, but raises the question how much we are willing to pay for the additional QALY gains. In such a scenario we therefore also consider a range of willingness-to-pay (WTP) ceilings while using the so-called acceptability curve, where the probability of cost-effectiveness is plotted against various WTP ceilings. The incremental cost-effectiveness ratios (ICER) acceptability curve helps in the decision whether ZemCAD should or should not be considered as cost-effective from a probabilistic medical decision-making perspective. The health-economic evaluation is completed with sensitivity analyses focusing on uncertainties in major cost-drivers, and is intended to show how robust the results of the cost-effectiveness analysis are under uncertainty. It is worth re-emphasising that in addition to health-economic considerations other considerations, such as medical-ethical considerations and patients’ preferences, ought to play a role in medical decision-making.

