### Measurements

At baseline demographics are measured. Measurements take place 6, 12, and 18 months after baseline. Quality of life is measured with the World Health Organization Quality of Life instrument, Brief version (WHOQOL-BREF) [25, 26]. The WHOQOL-BREF measures the overall quality of life in four different areas: physical health, psychological health, social relationships and environment. Anxiety symptoms are measured with the Beck Anxiety Inventory (BAI) [27], a validated self-rated questionnaire to assess the severity of anxiety symptoms. Depression severity is measured with the Patient Health Questionnaire (PHQ-9) [28, 29], a validated self-rated questionnaire to assess the severity of depression symptoms. Empowerment is assessed using the Dutch Empowerment Scale (Nederlandse Empowerment Vragenlijst) [30]. Contacts with health care professionals, medical costs, and productivity costs are measured with the Trimbos and Institute of Medical Technology Assessment questionnaire for costs associated with psychiatric illness (TiC-P) [31]. Using this self-completion questionnaire, direct and indirect costs of health care utilization of patients can be assessed. In addition, the EuroQoL (EQ-5D) [32] is used to compute Quality Adjusted Life Years (QALYs) gained, to be used in the cost-utility analysis.

To get insight in self-management strategies used by patients with chronic and treatment resistant anxiety or depressive disorders, and experiences of patients with a change of care setting, a questionnaire is designed. We do this by organizing focus groups, and use concept mapping [33] for processing the data. The questionnaire is administered during the ZemCAD trial, to all participants, in both conditions. An overview of measurements is provided in Table 1.

**Table 1 Tab1:** Overview of measurements

	Baseline	6 months	12 months	18 months
Demographics	x			
Clinical depression/anxiety (MINI)	x			
Quality of life (WHOQOL-BREF)	x	x	x	x
Anxiety (BAI)	x	x	x	x
Depression (PHQ-9)	x	x	x	x
Empowerment (Dutch Empowerment Scale)	x	x	x	x
Health care costs (TiC-P)	x	x	x	x
Health care costs (EQ-5D)	x	x	x	x
Questionnaire about self-management strategies and experiences with a change of care setting				x

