### Sample size

The feasibility of our trial is evaluated in a pilot study, which was carried out within one of the participating mental health services. Based on the number of included patients in this pilot and the number of services participating, we expect to be able to include 130–180 patients in our trial. This is enough to detect a standardized mean difference of d ≥ 0.50 in a 2-tailed test at *α* = 0.05 and with a power of (1-β) = 0.80. However, we do not expect such large differences between the conditions on any of the outcomes. With regard to the hypotheses about the clinical effects we assume non-inferiority rather than superiority and with *n* = 130 the non-inferiority margin would be as large as *d* = 0.45 (one sided), which is uninformative. That said, our main hypothesis requires health-economic decision-making. In that context it is more customary to take a probabilistic medical decision-making approach and do not rely on statistical techniques to test hypotheses.

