### Statistical analysis

Descriptive statistics are used for presenting the demographics of the sample. All outcome analyses are conducted in agreement with the intention-to-treat (ITT) principle, as required by the CONSORT statement [34]. To that end, we use linear mixed-effects models. If differences in baseline data are present, we adjust for relevant baseline characteristics, by including baseline variables as covariates in the model. To see how effects develop over time we also model interactions of the treatment with time in the linear mixed-effects models. All analyses are conducted in SPSS 22 and Stata 13.1 or later versions.

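### The only baseline-adjustment rule depends on observed imbalance and is worded for the mixed models, so adjustment of the main cost and QALY comparison for baseline EQ-5D and TiC-P is not fixed in advance

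*Protocol article*

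**What the plan says.** The Sample size section of the protocol article gives the economic comparison priority: "our main hypothesis requires health-economic decision-making". The Economic evaluation section describes how that comparison is made. On effects it says "The difference between ZemCAD and CAU in terms of health gains are expressed in QALYs, based on the EQ-5D", and on inference "Non-parametric bootstrapping is used to estimate the uncertainty surrounding costs and effects". The bootstrap results are read as probabilities over the four combinations of cost and QALY gain or loss, and through an acceptability curve. The section mentions no covariate.

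Baseline adjustment appears once, under Statistical analysis. That section begins with a general commitment, "All outcome analyses are conducted in agreement with the intention-to-treat (ITT) principle", and continues "To that end, we use linear mixed-effects models". The rule follows: "If differences in baseline data are present, we adjust for relevant baseline characteristics, by including baseline variables as covariates in the model".

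The two natural covariates are available. Table 1 under Measurements has a row beginning "Health care costs (TiC-P" and one beginning "Health care costs (EQ-5D", each marked at baseline and at 6, 12 and 18 months. (The text above the table makes clear that the EQ-5D supplies the QALYs, despite its row label.) According to Recruitment and randomization, the baseline questionnaire is completed before allocation, so both measures precede treatment.

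**The concern.** The decision rests on where the bootstrapped cost and QALY differences fall. Whatever shifts or widens that distribution changes the stated probability of cost-effectiveness directly, because no hypothesis test stands between the estimate and the conclusion.

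Baseline utility matters in two ways. If QALYs are computed as an area under the utility curve from baseline, baseline utility is itself part of the total. It can also be expected to predict later utility in the same patient. Baseline costs can be expected to predict later costs in patients with a long history of specialist care. With 130 to 180 patients, and blocking described only as a way to spread the arms over nurses, some chance imbalance in either variable is likely.

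A rule that adjusts only if differences are present handles this poorly. It leaves the choice of estimator until after the baseline data have been seen. Where the arms look balanced, it also gives up the precision that a prognostic covariate provides.

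**Working it through.** **1. The two readings of the text**

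| Reading | Consequence for the main comparison |
|---|---|
| The rule covers only the mixed models, as its reference to the model suggests | No adjustment of costs or QALYs is stated |
| The rule extends to the economic evaluation, as the phrase about all outcome analyses might suggest | Costs and QALYs are adjusted only if baseline differences are observed |

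Neither reading gives an adjustment fixed before the data are seen.

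**2. The plan's own figure**

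The article gives no figure for the cost-utility analysis. Its sample-size statement supplies the number per arm and can be reproduced. For d = 0.50, two-sided alpha 0.05 and power 0.80, n per arm = 2 × (1.960 + 0.842)² / 0.50² = 62.8, so 63 per arm or 126 in total (64 per arm, 128 in total, with the t distribution). Power at 65 per arm is 0.81. The lower end of the planned range, 130, is consistent with this and is used below.

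**3. Shift from a chance imbalance in baseline utility**

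Inputs:
- From the article: visits at 0, 6, 12 and 18 months, and N = 130.
- Assumed, because the article gives no values: 1:1 allocation (65 per arm), trapezoidal QALYs, utility SD 0.20 to 0.30, and a slope b of each follow-up utility on baseline utility of 0.4 to 0.6.

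Trapezoidal weights in years are 0.25, 0.50, 0.50 and 0.25, which sum to 1.5. The three follow-up weights sum to 1.25.

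Standard error of the baseline difference = SD × √(2/65) = SD × 0.1754:
- SD 0.20: 0.035
- SD 0.30: 0.053

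Shift in the unadjusted QALY difference = imbalance × (0.25 + 1.25 × b):
- b = 0.4: multiplier 0.75
- b = 0.6: multiplier 1.00

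For a one-standard-error imbalance, the lowest value is 0.0351 × 0.75 = 0.026 and the highest is 0.0526 × 1.00 = 0.053.

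**4. Precision given up**

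Assume equal variance at each visit and an equal correlation ρ of 0.3 to 0.7 between all visits, so that b = ρ. Then
- variance of an individual QALY = SD² × (0.625 + 1.625ρ)
- squared correlation of baseline utility with the QALY = (0.25 + 1.25ρ)² / (0.625 + 1.625ρ)

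The squared correlation is the proportional reduction in the variance of the QALY difference from adjustment:
- ρ = 0.3: 0.625² / 1.1125 = 0.35
- ρ = 0.5: 0.875² / 1.4375 = 0.53
- ρ = 0.7: 1.125² / 1.7625 = 0.72

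Over SD 0.20 to 0.30, the standard error of the QALY difference is 0.037 to 0.070 unadjusted and 0.025 to 0.045 adjusted. With this wider range of slopes, the one-standard-error shift is 0.022 to 0.059 at N = 130 and 0.019 to 0.050 at N = 180.

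**5. Costs**

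The same reasoning applies, with a variance reduction equal to the squared correlation between baseline and follow-up costs. The article gives nothing from which to put a number on it.

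**The case against.** The strongest objection is that the article does not say what a critic might read into it. A reader might infer that raw cost and QALY differences are bootstrapped. The text does not support that: the bootstrap sentence says how uncertainty is estimated, not which estimator is resampled, and a bootstrap can be run around a regression-adjusted difference. A reader might also infer that patients with a missing visit are dropped, so that the economic analysis breaks the intention-to-treat commitment. The article does not say so. A mixed model fitted to the utilities at each visit uses incomplete patients, and the QALY difference is then a linear combination of its visit estimates. The handling of missing visits is, besides, a detail that an article normally leaves to the analysis plan. Neither inference is part of this point.

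It can further be said that an adjustment rule exists and is aimed at baseline imbalance, and that covariate lists belong in the analysis plan. The absence of a list would indeed be no finding. But the condition on observed differences is stated text, and its wording ties it to another model. That part of the point stands.

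Lastly, an unadjusted difference is unbiased over repeated randomisations, and the bootstrap spread already contains the variation from chance imbalance. This is correct and limits the consequence. What remains is bias conditional on the imbalance that occurred, and a spread wider than it need be.

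**Conclusion.** The point holds as a weakness in how the main estimate is specified. The economic comparison either has no stated baseline adjustment or inherits one that depends on what the baseline data show, and always adjusting is better than both. Under the assumptions in the working, a one-standard-error imbalance in baseline utility at 65 per arm moves an unadjusted 18-month QALY difference by about 0.03 to 0.05, and adjustment removes roughly 35% to 72% of the variance of that difference. These sizes rest wholly on assumed SDs, slopes and correlations and on trapezoidal QALYs. The direction of the argument does not depend on the exact values, provided that baseline utility and baseline costs are prognostic. No figure in the article is wrong on this point, and the analysis would not be invalid without the change.

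**What to change.** In the Economic evaluation section, state that patients are resampled within arm and that, in each bootstrap sample, the QALY difference is estimated by regression on arm and baseline EQ-5D utility, and the cost difference by regression on arm and baseline TiC-P costs, regardless of observed balance. State also that the condition about baseline differences being present does not apply to this analysis. If the full protocol or analysis plan already fixes this, a sentence pointing to it is enough.

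The cost is one short paragraph and a few lines of code. No further data are needed, since both measures are already collected at baseline. The change should be made before outcome data are examined by arm.

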## Discussion

This article describes a protocol for a multicenter randomized controlled trial on the effectiveness and cost-effectiveness of a self-management intervention for patients with chronic and treatment resistant anxiety or depressive disorders in specialized outpatient mental health care. In this study we evaluate the cost-effectiveness of ZemCAD compared to CAU. We also explore the effects of the ZemCAD intervention compared to CAU on quality of life, depressive and anxiety symptom severity, and empowerment. Furthermore we like to shed light on the self-management strategies that patients use to cope with their chronic and treatment resistant anxiety or depressive disorder, and experiences of patients with a change of care setting. Given the fact that there are hardly any evidence-based interventions for patients with these disorders, and the need to make cost-effective use of scarce resources, the results of this study may provide a first ‘proof-of-concept’ in this under-researched but important field. Moreover the results of this study might be relevant for a large group of patients in the context of a transition of the Dutch health care system. In this study we focus on the transition from specialized outpatient mental health care to primary care.

## Abbreviations

BAI, Beck Anxiety Inventory; CAU, care as usual; EQ-5D, EuroQoL; ICER, incremental cost-effectiveness ratio; ITT, intention-to-treat; MINI interview, Mini-International Neuropsychiatric Interview; NEMESIS-2, Netherlands Mental Health Survey and Incidence Study-2; PHQ-9, Patient Health Questionnaire; QALYs, Quality Adjusted Life Years; TiC-P, Trimbos/iMTA questionnaire for Costs associated with Psychiatric illness; WHOQOL-BREF, World Health Organization Quality of Life instrument Brief version; WTP, willingness-to-pay; ZemCAD (English SemCAD), Self-management for Chronic Anxiety and Depression
